#### Methods for additional analyses (e.g., subgroup analyses) {20b}

Patient subgroups will be analysed according to treating hospital and liver function (i.e., Child–Pugh score).

#### Methods in analysis to handle protocol non-adherence and any statistical methods to handle missing data {20c}

Data produced following protocol non-adherence will not be included in the trial and will be disclosed. All researchers will make an effort to reduce missing data to a minimum. We will handle missing data with multiple imputation (MICE Package, R ver. 4.0.3, The R Foundation for Statistical Computing, Vienna, Austria). Missing values will be handled appropriately following established guidelines [11].

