#### Criteria for discontinuing or modifying allocated interventions {11b}

Patients who are assigned to the combination therapy group and do not receive RFA within 2 days after second TACE without consent of the investigator will be excluded. However, RFA can be delayed up to 1 month for patients with severe post-embolization syndrome depending on the hepatologist’s discretion.

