#### Outcomes {12}

The primary endpoint is 4–6-week CR in patients with viable tumour after first TACE. Tumour response rate will be evaluated in accordance with mRECIST [8]. In patients with multiple tumours, the sum of the largest diameters of viable lesions will be calculated.

Secondary outcomes include the following: (1) progression-free survival, defined as the time between random allocation and first progression; (2) overall response rate, defined as CR + partial response; (3) number of treatments (i.e., TACE) until achieving CR; (4) overall survival rate (i.e., 6, 12, and 24 months) and cause of death; and (5) change in liver function within 6 months based on liver function tests and Child–Pugh score.

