#### Sample size {14}

A previous study reports that the rate of CR after combination TACE and RFA therapy was 53% for patients with HCC tumours > 5 cm [9]. By contrast, the CR rate after TACE monotherapy was 26% for patients with intermediate-stage HCC [10]. Thus, we assume that the difference in CR rate between groups may be 28%. In this trial, we calculated that 48 patients per group are needed to achieve a two-sided α level of 0.05 and statistical power of 80%. A total of 120 patients will be included in this trial (i.e., 60 patients per group) to account for a 20% dropout rate (PASS, version 16, NCSS statistical software). Data will be analysed on an intention-to-treat basis according to patients’ originally assigned group.

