#### Plans to promote participant retention and complete follow-up {18b}

Patients will receive a recommendation to continue follow-up care at their treating hospital. There are no plans to promote participation retention.

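### The blanket multiple-imputation rule does not separate scans missing for unrelated reasons from scans missing through early treatment failure, so failed patients could be imputed a chance of complete response

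*Protocol article*

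**What the plan says.** Item 20c of the protocol article states "We will handle missing data with multiple imputation" and names the software package. The next sentence defers to a cited guideline for appropriate handling. Neither sentence names an endpoint, an imputation model or a reason for missingness that is treated differently.

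Item 12 defines the outcome: "The primary endpoint is 4–6-week CR in patients with viable tumour after first TACE". The follow-up section and item 17a make this an MRI judgement by blinded readers under mRECIST. No section gives a CR status to a randomised patient who has no such MRI.

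Three further statements decide who is in the analysis:
- Item 14 analyses patients by intention to treat in their assigned group, and enlarges the sample "to account for a 20% dropout rate".
- Item 11b says that combination patients who "do not receive RFA within 2 days after second TACE without consent of the investigator will be excluded".
- Item 20c opens with "Data produced following protocol non-adherence will not be included in the trial and will be disclosed".

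**The concern.** CR is a responder endpoint read at one time. If a scan is lost or unreadable, there is a true response that was not seen, and imputation is a reasonable way to estimate it. If the patient died or failed clinically before the scan, there is no unseen response to recover: the patient did not reach CR. The stated rule treats both cases alike.

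The reason for a missing scan may also depend on the arm. Only the combination arm has a second invasive procedure between second TACE and the MRI, and the protocol allows it to be delayed by up to a month. The protocol itself recognises early harm as possible: item 21a lists procedure-related death among the grounds for recommending cessation, and the Discussion mentions a risk of hepatic failure when TACE is used for a high tumour burden. If early harm were more frequent in the combination arm, imputing from the patients who were well enough to be scanned would turn part of that harm into responses in the same arm.

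**Working it through.** **Inputs.** From item 14: CR 53% (combination) and 26% (TACE), two-sided alpha 0.05, power 80%, 48 per group, 20% dropout, 60 per group. Assumed, because the documents give no figure: the share f of each arm with no MRI because of treatment failure, taken as 5%, 10% and 20%. Also assumed: 53% and 26% are the rates among scanned patients, and imputation without informative auxiliary variables returns about those rates.

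**The plan's own figure.** With unpooled variance, n = (1.960 + 0.842)² × (0.53×0.47 + 0.26×0.74) / 0.27² = 47.5, so 48 per group. Then 48 / 0.80 = 60 per group and 120 in total. The stated sample size reproduces and is not in dispute here.

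**The two ways of counting.** With observed rate p and failure share f:
- imputation at the arm rate reports p(1 − f) + p·f = p;
- counting failures as non-CR reports p(1 − f);
- the overstatement of the difference is therefore 0.53·f(combination) − 0.26·f(TACE).

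| Assumed failures before MRI | CRs imputed to failed patients, of 60 (combination / TACE) | Difference with imputation | Difference with failures as non-CR | Overstatement |
|---|---|---|---|---|
| 5% in both arms | 1.59 / 0.78 | 27.0 | 25.65 | 1.35 |
| 10% in both arms | 3.18 / 1.56 | 27.0 | 24.3 | 2.7 |
| 20% in both arms | 6.36 / 3.12 | 27.0 | 21.6 | 5.4 |
| 10% in combination only | 3.18 / 0 | 27.0 | 21.7 | 5.3 |
| 20% in combination only | 6.36 / 0 | 27.0 | 16.4 | 10.6 |
| 10% in TACE only | 0 / 1.56 | 27.0 | 29.6 | −2.6 |

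Differences are in percentage points. At these rates the overstatement is positive unless failure in the TACE arm is more than 0.53 / 0.26 = 2.04 times as frequent as in the combination arm.

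**With no true difference.** Suppose CR with failures counted as non-CR is 26% in both arms. Equal failure rates inflate both arms equally, and no false difference appears. If failures occur only in the combination arm, imputation reports 0.26 / (1 − f) there. The false advantage is 0.26 / (1 − f) − 0.26 = 1.4, 2.9 and 6.5 points at f = 5%, 10% and 20%.

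**Power.** By the pooled normal approximation, 60 scanned patients per arm give 86.6% power at 53% vs 26%. With failures counted as non-CR in both arms, power is 83.6%, 80.2% and 72.6% at 5%, 10% and 20%. So the 80% target still holds at 10% failure, but not at 20%. These figures show what the planned sample supports under that counting rule; they do not measure the bias.

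**The case against.** The strongest reply is that the text is general and silent, and is being read unfavourably. It nowhere says that a CR will be assigned to a patient known to have failed, and it does not say that an early death is missing data. If the outcome of a dead patient is regarded as known, nothing is imputed. A reader might infer that the sponsor intends to impute responses for failures; the documents do not support that.

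Second, the imputation model, the classification of early events and sensitivity analyses are commonly left to an analysis plan, which may exist. That is fair for the detail. It does not dispose of the point, because the protocol does state a rule, without exception, and the rule does not suit a responder endpoint. The deferral to a guideline sets no different rule for these patients.

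Third, several limits stand in full:
- A patient who decompensates or has toxicity but is still scanned has an observed response, and nothing is imputed.
- Some patients who stop before RFA may be excluded under items 11b and 20c instead of being imputed. That is a separate tension with intention to treat.
- Laboratory values and tumour markers are collected and could enter the imputation model, which would reduce the bias. None is named as a predictor.
- Eligibility (Child–Pugh score up to 8, performance score 0 or 1, no grade 3 or higher event after first TACE) may make early failure uncommon.
- The 20% dropout allowance is not an estimate of treatment failure, so the 20% rows are an extreme. The absence of a retention plan (item 18b) concerns follow-up and is not evidence of early failure.

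**Conclusion.** The point holds conditionally. If the imputation rule is applied as written to the binary CR endpoint under intention to treat, patients without the primary MRI because of early failure would receive a non-zero chance of a response they did not have.

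The size depends on a failure rate that the documents do not give. At an assumed 5–10% in both arms the difference is overstated by about 1.4 to 2.7 points, which is modest against 27. At 20% in both arms it is 5.4 points.

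A reader might infer that the trial is biased towards the combination. That goes too far. With a true difference at the planning rates, the overstatement favours the combination unless failure is about twice as frequent under TACE. A false advantage where none exists arises only if failure is more frequent in the combination arm. That is plausible given its extra procedure, but nothing in the documents shows it.

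**What to change.** In items 12 and 20c:
1. State that a randomised patient without the primary MRI because of death, clinical failure (including hepatic failure or clinical progression) or withdrawal for an adverse event counts as non-CR. Patients who were scanned keep their observed response.
2. Limit multiple imputation of the primary endpoint to scans missing for unrelated reasons, for example lost or unreadable.
3. Add a sensitivity analysis that counts every missing primary MRI as non-CR.
4. Reconcile the exclusion in item 11b and the removal of data after non-adherence in item 20c with the intention-to-treat statement in item 14. If a patient stays in the denominator while later data are dropped, even an observed non-CR could become a value to impute.

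The cost is a change of wording and one case-report field for the reason a scan is missing. No extra patients or procedures are needed. The downside is slightly lower reported CR rates. Recruitment is expected to run to about June 2026, so the protocol's stated timeline leaves room to make the change before the analysis.

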#### Plans to give access to the full protocol, participant level-data, and statistical code {31c}

The full protocol will be available on the registry website and is published here.

### Oversight and monitoring

#### Composition of the coordinating centre and trial steering committee {5d}

[name] and [name] will take full responsibility for scientific validity, study quality, study conduct, procedures, patient management after AEs, and the quality of the final trial results and reports. All investigators will share information through periodic meetings and will discuss appropriate trial management when problems occur. This study will be conducted without set up of Trial Steering Committee or Stakeholder and Public Involvement Group.

#### Composition of the data monitoring committee, its role, and reporting structure {21a}

A data monitoring committee (DMC) will be constituted by three independent medical researchers ([name]; Institute of Biomedical Science, Catholic Kwandong University International St. Mary’s Hospital, Incheon, Korea, [name]; Department of Internal Medicine, Incheon St. Mary’s Hospital, The Catholic University of Korea, Incheon, Korea, [name]; Department of Radiology, Bucheon St. Mary’s Hospital, College of Medicine, The Catholic University of Korea, Seoul, Korea). The DMC will check the appropriateness of source documents, patient compliance, protocol violations, the process of consent acquisition and storage, review of e-CRFs and investigators’ binders, collection of information on AEs, and follow-up procedures. The committee will be responsible for protecting participant safety, evaluating trial effectiveness, making decisions on trial conduct or cessation, and advising on protocol improvement.

Any procedure-associated AEs will be checked during the follow-up period and recorded in the e-CRFs. In the case of serious AEs (grade ≥ 3), AEs will be reported to the principal investigator ([name]) within 24 h. Each DMC member will judge whether the AE is associated with the investigated therapy, and any related serious AEs will immediately be reported to the IRB and principal investigator. Each researcher should report any serious AEs or other unexpected problems to the IRB within 15 working days. The DMC can recommend cessation of the trial if one treatment group has significantly more AEs than the other treatment group, the occurrence of serious AEs including procedure-related death, or complete enrolment of participants earlier than expected.

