#### After allocation

All patients will undergo second TACE for the viable portion of the HCC with ethiodized oil and Gelfoam particles. Interventional radiologists performing second TACE will be blinded to patient allocation, and TACE will be performed in a conventional manner.

Patients in the combination TACE and RFA therapy group will be treated with additional RFA of the viable portion of the tumour under the guidance of fusion images from ultrasound and CT. RFA will be implemented within 1–2 days after second TACE. Whether RFA can be delayed for up to 1 month will depend on the medical condition of the patients. RFA will be performed by physicians at the three hospitals with more than 8 years of experience. A 17-gauge radiofrequency electrode system including three electrodes with a length of 150 mm and a 30-mm ablation zone (Octopus; STARmed, Goyang-si, Korea) will be used. The number of electrodes used will be determined based on the size of the viable tumour and the physicians’ discretion. However, physicians will attempt to obtain an ablation margin of at least a 1-cm perimeter around the viable tumour.

Patients in the TACE monotherapy group will be discharged from the hospital without further intervention if they experience no AEs.

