#### Adverse event reporting and harms {22}

AEs will be classified according to CTCAE [12]. Any serious AE (i.e., grade ≥ 3) will be reported to the IRB. Daily checks for each patient will be conducted by the research team at each hospital and communicated with the other research teams.

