Treatment of beyond-the-Milan criteria HCC is clinically challenging due to the size and number of tumours and the possibility of metastasis and vascular invasion. Patients with beyond-the-Milan criteria HCC have not been candidates for ablation therapy, and guidelines instead recommend sorafenib treatment. However, local treatments such as TACE applied before systemic treatment have been attempted because some patients with intermediate-stage disease show better responses to localized treatment and can succeed in downstaging compared with patients receiving systemic treatment. However, TACE with tumours > 5 cm often leaves a viable portion of tumour requiring repeated treatment [9]. MRI ~ 1 month after TACE can detect the viable portion of HCC, which can be smaller than its initial size and possibly treatable by RFA.

This trial protocol has some limitations. First, this is an open-blind study, although patients will be blinded up to their completion of second TACE. Second, the mechanism by which combination therapy may confer a survival benefit is unclear, and the magnitude of the survival benefit compared with that following monotherapy may be more limited than expected. Third, advanced-stage tumours have a high possibility of vascular invasion that can fail to be revealed by imaging, leading to worse prognosis than expected in these patients.

In summary, this trial will evaluate the efficacy and safety of combination TACE and RFA therapy versus TACE monotherapy among patients with viable beyond-the-Milan criteria HCC after first TACE.

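### Adverse events are filtered by attribution before recording in an open trial, and serious is defined by CTCAE grade, so the between-arm safety comparison is open to unequal ascertainment and lower-grade serious events escape expedited reporting

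*Protocol article*

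**What the plan says.** The rules on adverse events sit mainly in two sections of the protocol article.

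- **Recording** (Composition of the data monitoring committee {21a}): "Any procedure-associated AEs will be checked during the follow-up period and recorded in the e-CRFs". This is the only sentence that says which AEs enter the e-CRF.
- **Relatedness** (same section, after the reporting step): "Each DMC member will judge whether the AE is associated with the investigated therapy".
- **Serious events** (same section): "In the case of serious AEs (grade ≥ 3), AEs will be reported to the principal investigator", within 24 h. Adverse event reporting and harms {22} repeats the definition: "Any serious AE (i.e., grade ≥ 3) will be reported to the IRB". Section {21a} also asks each researcher to notify the IRB of serious AEs or other unexpected problems within 15 working days, with no limit by relatedness.
- **Use of the data**: the DMC can recommend cessation "if one treatment group has significantly more AEs than the other treatment group". The Discussion closes by saying that "this trial will evaluate the efficacy and safety of combination TACE and RFA therapy".
- **Blinding** ({16b}, {17a}, {17b}): the hepatologist knows the allocation from randomisation, and it is disclosed once second TACE is finished. Only the independent imaging assessors are described as blinded beyond that point.

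**The concern.** A safety comparison between arms needs the same rule for what is counted in each. Here an event must first be judged procedure-associated before it is recorded, and after second TACE the treating team knows the arm. In the combination arm the event can be ascribed to TACE or RFA; in the monotherapy arm only to TACE. The same late infection or liver decompensation could be entered for one patient and left out for another, purely on attribution. A committee that judges relatedness later cannot judge an event that was never entered.

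The definition of serious is a separate fault. Grade describes how severe an event is; seriousness describes its consequence, such as death or a longer hospital stay. If grade stands in for seriousness, an event with a serious consequence but a lower grade does not reach the principal investigator by the 24 h route.

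At stake are the DMC's cessation ground and the safety conclusion that the Discussion promises.

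**Working it through.** The protocol states no AE rate, so it has no figure on this point to reproduce. The check is mainly a reading of the text.

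**1. Order of attribution and recording.** In {21a} the recording sentence applies the association filter first. The later sentence has the DMC judge association, which presupposes that unassociated events have also been reported. The serious-event sentences carry no relatedness limit. The section thus has two incompatible orders: filter then record, and report then judge. For serious events the second order gives some protection. For other events only the first applies.

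**2. Who attributes, and knowing what.** The protocol does not say who decides that an event is procedure-associated for e-CRF entry. Data management {19} makes the investigators responsible for entering data, and allocation is open after second TACE. So the filter can be applied with knowledge of the arm. Procedures available for attribution after randomisation: TACE and RFA (2) against TACE (1).

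**3. Path of an event that is serious by outcome but below grade 3.**

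| Step | Included? |
|---|---|
| e-CRF | Yes, if judged procedure-associated |
| DMC count of AEs | Yes, if recorded; the cessation ground has no grade limit |
| 24 h report to the principal investigator | No |
| IRB report as a serious AE | No |
| IRB report as an unexpected problem | Only if someone so classifies it |

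**4. Could unequal capture matter at this sample size?** This is illustration only. Assumptions, none from the documents: each patient counts once (any recorded AE or none), true risk is equal in both arms, capture is complete in the combination arm, and the test is two-sided at 5%. The arm size is the protocol's 60, which follows from its 48 per group and 20% dropout: 48 / (1 − 0.20) = 60.

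With recorded proportions a (combination) and b (monotherapy), p = (a + b)/2, s0 = √(2p(1 − p)/60) and s1 = √((a(1 − a) + b(1 − b))/60), the chance of a significant difference is

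1 − Φ((1.96·s0 − (a − b))/s1) + Φ((−1.96·s0 − (a − b))/s1).

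Example with true risk 40% and monotherapy capture 80%: a = 0.40, b = 0.32, p = 0.36, s0 = 0.0876, s1 = 0.0873. The first term is 1 − Φ(1.05) ≈ 0.147 and the second about 0.002, giving 14.9%.

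| True AE risk | Capture 100% | 90% | 80% | 70% |
|---|---|---|---|---|
| 20% | 5.0% | 5.9% | 8.8% | 14.0% |
| 40% | 5.0% | 7.3% | 14.9% | 28.2% |
| 60% | 5.0% | 10.1% | 26.0% | 50.5% |

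Under these assumptions the chance of a spurious difference runs from barely above 5% to about one in two. The documents do not say where in this range the trial lies, or whether it lies there at all.

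**The case against.** The strongest reply is that the safeguards are wider than the recording sentence suggests. Serious AEs and unexpected problems go to the IRB whatever their cause, so a grade 3 infection judged unrelated is still reported. The DMC is described as independent, checks source documents and e-CRFs, and is the only body named as judging association. Change in liver function and cause of death are secondary outcomes in both arms. More AEs caused by the added RFA are a treatment effect that the comparison should show. The DMC recommends; nothing stops automatically. All of this stands. It means that unattributed serious events are not simply lost, and that 2 procedures against 1 is not a measure of bias. It does not reconcile the recording sentence with the later ones, and it gives no route into the e-CRF for a non-serious event judged unrelated.

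A reader might also infer more than the text supports:

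- *That surveillance lasts longer in the combination arm.* Section {22} says "Daily checks for each patient will be conducted by the research team at each hospital", with no duration, no arm difference and no tie to the inpatient stay.
- *That monotherapy patients go without contact until the imaging visit.* Those who "will be discharged from the hospital without further intervention if they experience no AEs" leave earlier, but Follow-up and primary endpoint evaluation gives all patients the same 4–6 weeks of outpatient follow-up.
- *That the DMC comparison misses lower-grade serious events.* The cessation ground counts AEs of any grade, so a recorded lower-grade event is in it. It is missed as serious, not as an AE.
- *That leaving AEs out of the endpoint lists is an error.* Harms have their own section, and listing them as an outcome is a reporting preference.

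Finally, how often an event that prolongs hospitalisation would be graded below 3 depends on the cited CTCAE text, which is not at hand.

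**Conclusion.** The concern holds in two parts. First, the recording rule in {21a} filters on attribution before entry, conflicts with the later sentences of the same section, and operates with allocation known. This leaves the between-arm AE comparison open to unequal ascertainment. That it happens, in which direction and how far cannot be shown from the documents; the table in the working rests wholly on assumed risks and capture rates. Second, sections {21a} and {22} define serious by grade. An event serious by outcome but below grade 3 falls outside the 24 h report, and outside IRB serious-AE reporting unless it is handled as an unexpected problem. This follows from the wording and needs no rate; how many events it affects is unknown. Both are stated rules rather than details left to a fuller document, and both merit an amendment. The conclusion does not extend to a demonstrated bias or to a difference in surveillance between arms.

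**What to change.** Amend {21a} and {22} as follows:

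1. Reconcile the sentences in {21a} so that all AEs in both arms, from second TACE to the 4–6-week visit, are entered in the e-CRF regardless of attribution, with relatedness as a separate field judged afterwards.
2. Define serious by outcome (death, threat to life, hospitalisation or its prolongation, disability), and keep CTCAE grade as a separate severity field.
3. State that the DMC's between-arm comparison uses all recorded AEs.

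The cost is a protocol and e-CRF amendment and a modest increase in AE recording. No new procedure or visit is needed. Trial status puts the end of recruitment at about June 2026, so later patients would benefit. Because recruitment began in November 2020, the date of the change should be kept in the dataset so that AEs recorded under the two rules can be told apart.
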